#### Secondary outcome measure: incidence of gastrointestinal and respiratory infections in children

The secondary outcome measure is the incidence of gastrointestinal and respiratory infections in children attending DCCs. The aim is that 600 parents will monitor disease incidence in their child using strict definitions for diarrhea and a cold. Diarrhea is defined as at least two watery or unusually loose bowel motions in 24 hours
[15]. A cold is defined as a blocked or runny nose with at least one of the following symptoms: coughing, sneezing, fever, sore throat, or earache.

Disease incidence will be assessed by parents using a paper calendar to mark the days their child has diarrhea and/or a cold. Each calendar page includes the definitions of illness. The paper calendar will facilitate record keeping and minimize recall bias. Parents will be contacted every two weeks by email and by regular post to enter the calendar page in an online version of the calendar or to send it in by regular post using a free-of-charge return envelop. The email will contain a link to the online calendar and parents will receive a password to ensure confidentiality. Parents who do not respond will receive a reminder email after one week, after two weeks they will receive a reminder letter, and after three weeks, if by then they still have not replied, they will be contacted by telephone. Monitoring of disease incidence by parents will last six months during which the intervention will be implemented in phases and baseline and follow-up data will be collected. In total, parents will be asked to return 14 calendar pages, with each page covering two weeks. To stimulate response parents will receive small incentives during the six months data collection (e.g. inflatable beach ball) and parents who return all calendar pages will receive a larger incentive at the end of the trial (i.e. tickets for the whole family for an amusement park for children).

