### Intervention implementation and data collection

The intervention will be implemented in the 36 intervention DCCs in phases over a period of six months. Timing of the intervention will be during the winter months, namely from mid-September until the end of March, when most gastrointestinal and respiratory infections occur. In all participating DCCs (both intervention and control), data will be collected in two groups. In each intervention DCC, due to budget restrictions, only the two groups where data are collected will receive the HH products and refills for six months. To facilitate support from the management and to stimulate cultural changes concerning HH, the training sessions and posters/stickers will be offered to the whole intervention DCC.

Figure 1 shows the timeline of phased implementation of the intervention and data collection. Baseline compliance (T0) and baseline incidence rates will be collected prior to start of the intervention. The intervention will start with the delivery of the dispensers with refills and posters/stickers. Shortly after that the training to educate about the national HH guidelines will be given. Compliance will be observed again one month after start of the intervention (T1) and this will be followed by the first team training session. Compliance will then be observed once more three months after start of the intervention (T2) after which the second team training session will be given. The final compliance observations will take place after the second team training session and six months after start of the intervention (T3).

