### Data analyses

First, descriptive analyses will be performed to assess the effect of the intervention on observed HH compliance and on incidence of gastrointestinal and respiratory infections in children. Compliance with HH guidelines will be calculated by dividing the number of HH actions by the total number of opportunities for which HH is indicated according to the Dutch national guidelines. Incidence of gastrointestinal and respiratory infections will be calculated by dividing the number of illness episodes by the total number of days at risk.

To account for clustering of the data within caregivers/children and within DCCs, multilevel analyses will be performed. The effect of the intervention on observed HH compliance will be analyzed using multilevel logistic regression. Multilevel poisson regression will be used to analyze the effect of the intervention on incidence of gastrointestinal and respiratory infections in children. If necessary, baseline differences between intervention and control DCCs will be corrected for, as well as for possible confounders at the level of the DCCs, caregivers or children.

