#### Secondary outcome measure: incidence of gastrointestinal and respiratory infections in children

To be able to detect 25% reduction in incidence of gastrointestinal infections of three per year and 15% reduction in incidence of respiratory infections of nine per year, we would need a sample size of 60 DCCs (30 intervention and 30 control DCCs) and disease monitoring of 600 children (10 children per DCC) for six months. This is based on 80% power with a two-sided alpha of 0.05, assuming 10 children per DCC and taking into account clustering of data within children and within DCCs. The assumed reduction in disease incidence seems to be realistic, given the pooled estimates of 39% and 31% reduction in gastrointestinal illness
[7,25], and a pooled estimate of 21% reduction in respiratory illness
[25].

To be able to detect an effect of the intervention on both our primary and secondary outcome measure, it is necessary to include at least 60 DCCs in the cluster randomized controlled trial (30 intervention and 30 control DCCs) and include at least 600 children of which parents will monitor disease incidence for six months. However, some DCCs and some parents/children might withdraw from the trial due to unforeseen reasons. To allow for about 15% lost to follow-up, we aim to include five extra intervention DCCs and five extra control DCCs (in total 35 intervention and 35 control DCCs).

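### Secondary outcome: the six months of illness monitoring used for the power calculation include pre-intervention baseline days, and nothing in the analysis removes them from the infection rate

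*Protocol article*

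**What the plan says.** All references are to the protocol article.

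- **Outcome measures, secondary outcome:** monitoring "will last six months during which the intervention will be implemented in phases and baseline and follow-up data will be collected". The same paragraph asks parents for 14 pages of two weeks each.
- **Intervention implementation and data collection:** baseline incidence is collected before the intervention starts. The intervention is timed for the winter, "namely from mid-September until the end of March". The last compliance observation (T3) is six months after the start.
- **Sample size calculation, secondary outcome:** the requirement is 60 DCCs and "disease monitoring of 600 children (10 children per DCC) for six months", to detect a "25% reduction in incidence of gastrointestinal infections of three per year" and a "15% reduction in incidence of respiratory infections of nine per year". "This is based on 80% power with a two-sided alpha of 0.05, assuming 10 children per DCC", and clustering is said to be allowed for, but no value is given. Baseline time is not mentioned.
- **Data analyses:** incidence is obtained by "dividing the number of illness episodes by the total number of days at risk". A multilevel Poisson model follows. Baseline differences are corrected for only where that is judged necessary.

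**The concern.** The same six months serve two purposes. In the outcome section they hold both baseline and follow-up. In the sample size section they are all outcome time. The analysis section does not separate the two, because its denominator is every day at risk.

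In the pre-start days the intervention cannot have had an effect, so the true rate ratio there is 1. Averaging them into the outcome moves the estimated rate ratio toward 1 and lowers power. Infection incidence is also the outcome that sets the size of the trial: 60 DCCs, against 20 for hand hygiene compliance. A null infection result would then be hard to read, since part of the shortfall could come from the time window.

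The durations do not agree either. Fourteen two-week pages make 28 weeks, two weeks more than the 26 weeks in six months.

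**Working it through.** **1. Durations.** 14 × 2 = 28 weeks of pages. Mid-September to the end of March (15 September to 31 March) is 28.3 weeks. T3 is 26 weeks after the start. If the pages are to run up to T3, 28 − 26 = 2 weeks remain for baseline. With a 4-week baseline, illness follow-up would end two weeks before T3. The text does not give the baseline length, so I use 2 and 4 weeks as assumptions.

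**2. Inputs.** From the sample size section: two-sided alpha 0.05, power 80%, 30 DCCs per arm, 10 children per DCC for 0.5 year, so y = 5 child-years per DCC. Rates per child-year are 3.00 against 2.25 (gastrointestinal) and 9.00 against 7.65 (respiratory). (1.960 + 0.842)² = 7.849.

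**3. The plan's own figure.** Without clustering, child-years per arm = 7.849 × (λ0 + λ1)/(λ0 − λ1)².

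- Gastrointestinal: 7.849 × 5.25/0.75² = 73.3, or about 147 children for six months.
- Respiratory: 7.849 × 16.65/1.35² = 71.7, or about 143 children.

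The plan's 300 per arm therefore implies a design effect of about 2.05 and 2.09. The 80% cannot be checked independently, because no clustering value is stated. I take it as given and solve for the between-DCC coefficient of variation k in the cluster formula for rates:

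variance of the rate difference = [(λ0 + λ1)/y + k²(λ0² + λ1²)]/30

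- Gastrointestinal: [5.25/5 + k² × 14.06]/30 must equal 0.75²/7.849, so k ≈ 0.28.
- Respiratory: [16.65/5 + k² × 139.52]/30 must equal 1.35²/7.849, so k ≈ 0.16.

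Adding one cluster per arm as a small-sample correction changes k only slightly (0.27 and 0.16).

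**4. Baseline pages pooled into the rate.** For 28 weeks of pages with b baseline weeks, the average reduction is the stated one × (28 − b)/28, and y = 10 × 28/52 = 5.38. Power = Φ(difference/SE − 1.96).

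| Baseline | Outcome | Average reduction | Difference/SE | Power |
|---|---|---|---|---|
| 2 weeks | GI | 25% × 26/28 = 23.2% | 0.696/0.265 = 2.63 | 75% |
| 2 weeks | Respiratory | 15% × 26/28 = 13.9% | 1.254/0.476 = 2.64 | 75% |
| 4 weeks | GI | 25% × 24/28 = 21.4% | 0.643/0.267 = 2.41 | 67% |
| 4 weeks | Respiratory | 15% × 24/28 = 12.9% | 1.157/0.478 = 2.42 | 68% |

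**5. Baseline pages excluded, stated reduction afterwards.**

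- 2 weeks: 26 weeks remain, y = 5.00, power 80% for both outcomes.
- 4 weeks: 24 weeks remain, y = 10 × 24/52 = 4.62, power 78% for both.

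**6. Sensitivity to six months taken literally** (26 weeks in total, baseline inside it). Pooled: about 73% (2 weeks) and 65% (4 weeks). Excluded: about 78% and 77%.

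The comparison shows where the loss arises. Giving up a short baseline costs little; counting it as outcome time costs several times more.

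**The case against.** The strongest reply is that the protocol treats baseline as separate. It names baseline incidence rates collected before the start, distinguishes baseline from follow-up data, and allows for baseline correction. On this view the days-at-risk wording is only the generic definition of a rate, and 28 weeks of pages less a 2-week baseline leaves exactly the 26 weeks that the power needs. The timeline figure, not shown here, may give the baseline length. Much of this stands. Pooling is what the wording leads to if followed literally, but it is not declared as an intention, and an unstated baseline length is not held against the article. What remains is that three sections use the same six months in incompatible ways, and that the stated method makes use of the baseline optional.

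A reader might go further and infer that the phased roll-out reduces power much more. The second team session comes late: T2 is "three months after start of the intervention (T2) after which the second team training session will be given". Assuming half the effect in the first 13 weeks gives about 50–54% power. The documents do not support that. Products, posters and stickers arrive at the start and the guideline training shortly after, so only the team sessions are late. The 25% and 15% are not described as effects of the complete package, and they lie below the pooled estimates that the protocol cites (39% and 31%; 21%). They can be read as averages over the monitored period.

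**Conclusion.** The point holds as an inconsistency in the outcome window with a calculable consequence. If pre-start days are counted as outcome time, power falls from the stated 80% to about 75% with a 2-week baseline and 67–68% with a 4-week baseline. If they are excluded, it is about 80% and 78%. These figures rest on clustering back-solved to give exactly 80%, on assumed baseline lengths, on 28 weeks of pages, on 30 DCCs per arm, and on a constant background rate over the season. The 35 DCCs per arm are a reserve for dropout and are not counted as spare power.

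It does not follow that the stated power will not be delivered. Without a clustering value the 80% can be neither confirmed nor refuted, and one reading of the page count gives it back in full. The severity is moderate: the outcome is secondary, and the calculation for hand hygiene compliance is not affected.

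**What to change.** 1. Define the infection outcome on calendar pages after the start of the intervention only. For control DCCs, use the matching date, counted from T0, of intervention DCCs in the same randomization stratum, so that both arms are compared over the same part of the season.
2. Always include pre-start incidence as a baseline covariate in the multilevel Poisson model, in place of the optional correction.
3. Reconcile the six months of monitoring with the 28 weeks of pages and with T3 at six months after the start.
4. Restate the power for infections using post-start child-time, and say that 25% and 15% are the average reductions over that period.

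The cost is wording in the outcome, analysis and sample size sections. No new data are needed. With a baseline longer than two weeks, the restated power will be slightly below 80% (about 78% at 4 weeks, on the same assumptions).

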### Intervention implementation and data collection

The intervention will be implemented in the 36 intervention DCCs in phases over a period of six months. Timing of the intervention will be during the winter months, namely from mid-September until the end of March, when most gastrointestinal and respiratory infections occur. In all participating DCCs (both intervention and control), data will be collected in two groups. In each intervention DCC, due to budget restrictions, only the two groups where data are collected will receive the HH products and refills for six months. To facilitate support from the management and to stimulate cultural changes concerning HH, the training sessions and posters/stickers will be offered to the whole intervention DCC.

Figure 1 shows the timeline of phased implementation of the intervention and data collection. Baseline compliance (T0) and baseline incidence rates will be collected prior to start of the intervention. The intervention will start with the delivery of the dispensers with refills and posters/stickers. Shortly after that the training to educate about the national HH guidelines will be given. Compliance will be observed again one month after start of the intervention (T1) and this will be followed by the first team training session. Compliance will then be observed once more three months after start of the intervention (T2) after which the second team training session will be given. The final compliance observations will take place after the second team training session and six months after start of the intervention (T3).

**Figure 1 F1:**
[figure not shown]
Timeline of data collection and phased implementation of a hand hygiene intervention at child day care centers (DCCs).

### Blinding

DCCs will not be blinded to treatment arms; the managers will be informed whether their DCC is allocated to the intervention or control group. Although the observers who collect compliance data and parents who monitor disease incidence will not be informed whether the DCC is in the intervention or control group, they will probably recognize the intervention materials.

### Data analyses

First, descriptive analyses will be performed to assess the effect of the intervention on observed HH compliance and on incidence of gastrointestinal and respiratory infections in children. Compliance with HH guidelines will be calculated by dividing the number of HH actions by the total number of opportunities for which HH is indicated according to the Dutch national guidelines. Incidence of gastrointestinal and respiratory infections will be calculated by dividing the number of illness episodes by the total number of days at risk.

To account for clustering of the data within caregivers/children and within DCCs, multilevel analyses will be performed. The effect of the intervention on observed HH compliance will be analyzed using multilevel logistic regression. Multilevel poisson regression will be used to analyze the effect of the intervention on incidence of gastrointestinal and respiratory infections in children. If necessary, baseline differences between intervention and control DCCs will be corrected for, as well as for possible confounders at the level of the DCCs, caregivers or children.

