Compliance will be assessed with direct unobtrusive observation by trained observers before start of the intervention (T0) and one (T1), three (T2), and six (T3) months after start of the intervention. At each measurement time point (i.e. T0, T1, T2 and T3) the aim is to observe, during a single day in each DCC, three caregivers in the two groups participating in the study and to observe each caregiver for two hours. One observer will observe one caregiver at a time, as well as the children of which HH is supervised by that caregiver. Observations will take place during routine care activities in common rooms including the diaper-changing room, the kitchen and the indoor/outdoor playgrounds. The observers will collect data using personal digital assistants (PDAs) for electronic on-site data entry. Data will be collected using the World Health Organization HH observation method
[24], adapted for use in child DCCs.

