### Sample size calculation

#### Primary outcome measure: observed HH compliance

HH compliance is expected to increase due to the intervention from 30% at baseline to 60% six months after start of the intervention. To detect this increase we would need a sample size of 20 DCCs in a two-arm cluster randomized controlled trial (10 intervention and 10 control DCCs). This is based on 80% power with a two-sided alpha of 0.05, assuming 60 observed HH opportunities per DCC per measurement time point (i.e. T0, T1, T2 and T3) and taking into account clustering of data within DCCs.

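### If compliance at T0 to T3 is modelled jointly, the two clustering levels named leave out DCC-by-visit variation, and intervals for change or time-specific effects are too narrow

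*Protocol article*

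**What the plan says.** Under Data analyses, the protocol article names the levels of clustering: "To account for clustering of the data within caregivers/children and within DCCs, multilevel analyses will be performed". The model family follows: "The effect of the intervention on observed HH compliance will be analyzed using multilevel logistic regression". Baseline is handled conditionally: "If necessary, baseline differences between intervention and control DCCs will be corrected for".

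The section on the primary outcome sets the measurements "before start of the intervention (T0) and one (T1), three (T2), and six (T3) months after start of the intervention". At each of these, "the aim is to observe, during a single day in each DCC, three caregivers in the two groups participating in the study".

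The sample size section describes the target as a rise over time: "HH compliance is expected to increase due to the intervention from 30% at baseline to 60% six months after start of the intervention". It continues: "This is based on 80% power with a two-sided alpha of 0.05, assuming 60 observed HH opportunities per DCC per measurement time point".

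The article does not say whether the four time points enter one model or are compared one at a time, nor which contrast carries the primary result. It gives no ICC and no figure for variation between visits within a DCC.

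**The concern.** Everyone observed in a DCC at one visit shares that day: its staffing, its children and its illness load. DCCs may also move differently over the months. Each team sets its own goals, the components arrive in phases between visits, and all DCCs had feedback on their compliance six months before the trial, which may fade at different rates. This is variation of the DCC-by-visit kind.

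A DCC intercept describes a level that stays fixed over the four visits. A caregiver intercept describes differences between people. In a logistic model the lowest-level variance is fixed by the binomial distribution, so a visit-specific shift of a whole DCC has no proper place in the model. It is treated as noise that averages out over three caregivers and about 60 opportunities, which it does not do. Any effect measured within DCCs over time, such as the arm difference in change from T0 to T3, then gets a standard error (SE) that is too small. At stake is the stated confidence in the compliance result, if it is analysed in that way.

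**Working it through.** **The plan's own figure.** For 30% v 60%, 80% power and two-sided 0.05, the usual formula gives [1.96 x sqrt(2 x 0.45 x 0.55) + 0.842 x sqrt(0.30 x 0.70 + 0.60 x 0.40)]^2 / 0.30^2 = 42 opportunities per arm. With 60 per DCC, 10 DCCs per arm correspond to 42 x (1 + 59 x ICC) = 600, so ICC is about 0.22. As the article states no ICC, the total of 20 DCCs can be neither confirmed nor refuted. It also says nothing about variation between visits.

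**Inputs from the article.** 36 and 35 DCCs; four visits; three caregivers per visit; 60 opportunities per DCC per visit, hence 20 per caregiver; compliance 45%, midway between 30% and 60%.

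**Assumptions, logit scale.** DCC variance 0.4; caregiver variance 0.2; DCC-by-visit variance s from 0 to 0.4. For s from 0.05 to 0.4, the share of DCC variance that is stable over time, 0.4/(0.4 + s), runs from 89% to 50%.

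**Formulas for the arm difference in change from T0 to T3.** Binomial variance per caregiver: e = 1/(20 x 0.45 x 0.55) = 0.202. Arm factor: f = 1/36 + 1/35 = 0.0563.

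- Same caregivers at every visit. True variance: 2 x (e/3 + s) x f. Variance seen by the two-level model: 2 x (e/3) x f.
- New caregivers at each visit. True variance: 2 x [(0.2 + e)/3 + s] x f. The two-level model takes part of s into its caregiver variance. With 12 caregivers in four groups of three, that part is s x (12 - 36/12)/11 = 9s/11. Variance seen: 2 x [(0.2 + 9s/11 + e)/3] x f.

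Example, same caregivers, s = 0.4: model SE = sqrt(2 x 0.0673 x 0.0563) = 0.087; true SE = sqrt(2 x 0.4673 x 0.0563) = 0.229; ratio 0.38.

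Example, new caregivers, s = 0.4: model SE = sqrt(2 x 0.243 x 0.0563) = 0.166; true SE = sqrt(2 x 0.534 x 0.0563) = 0.245; ratio 0.68.

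Expected coverage of a nominal 95% interval is 2 x Phi(1.96 x ratio) - 1. The simulated column comes from Gaussian data on the logit scale fitted by REML, 400 runs per cell. It spans the T0-to-T3 contrast and a contrast of all follow-up visits in a model that includes T0.

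| s | Caregivers | SE ratio | Expected coverage | Simulated coverage |
|---|---|---|---|---|
| 0 | either | 1.00 | 95% | 94-96% |
| 0.05 | same | 0.76 | 86% | 81-87% |
| 0.1 | same | 0.63 | 79% | 77-78% |
| 0.2 | same | 0.50 | 67% | 67-70% |
| 0.4 | same | 0.38 | 54% | 55% |
| 0.05 | new | 0.90 | 92% | 91% |
| 0.1 | new | 0.83 | 90% | 90-91% |
| 0.2 | new | 0.75 | 86% | 85-90% |
| 0.4 | new | 0.68 | 81% | 81-82% |

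With a DCC-by-visit intercept added, simulated coverage was 93-97% in every cell.

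**A second simulation.** This used 3,000 null trials per scenario, compliance 42%, an assumed DCC ICC of 0.06 to 0.17 and 50-90% of DCC variance stable over time. A linear mixed model with a DCC random intercept was fitted to caregiver proportions. The arm x T3 test rejected in 6-19% of trials at a nominal 5%, with the SE understated by 3-33%. Testing the DCC-level change, or T3 adjusted for T0, gave about 4-7%.

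**Where the problem does not arise.** In a T3-only model with DCC and caregiver intercepts, simulated coverage was 94-95% at every s tried. The DCC intercept at a single visit contains s. A single arm effect pooled over T1 to T3, without T0 as an outcome, is a comparison between DCC means. In a balanced design its variance per DCC is 0.4 + s/3 plus the caregiver and binomial parts. All of this shows up in the spread of DCC means, which the DCC intercept picks up.

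**The case against.** The strongest reply is that the article never commits to the model that fails. It does not say that T0 to T3 enter together, that the test is arm x T3, or that the DCC effect is an intercept only. Correcting for baseline where needed reads more like adjustment for T0 than like T0 as an outcome row, and the sample size fixes the target at six months. A T3 comparison adjusted for T0, which is sound, is already permitted. A journal article also commonly leaves the exact random-effects structure to the full plan.

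Much of this stands. A reader might infer that the type I error of the primary result is inflated as planned. The article does not support that, because it requires a joint model, a within-DCC contrast and visit variance above zero, and none of these is stated. A reader might also extend the point to infections. Those are parent-reported episodes per days at risk, with no single-day visits. Nothing says that baseline and follow-up periods share one model, and no calculation was made for them, so they are left out here.

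The size is also open. At the mild end of the second simulation, 6% rejection lies within the 4-7% seen for the sound methods. It would be wrong to say that visit variation must dominate the error.

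What remains is that the article is not silent on clustering. It names two levels, and they are not enough for a joint model. Such a model is a natural reading of a plan with four measurements, no designated time point and a target worded as a rise from baseline.

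**Conclusion.** The point holds conditionally. If compliance at T0 to T3 is analysed in one model with only DCC and caregiver intercepts, and the effect is a change or a time-specific contrast, intervals are too narrow whenever DCC-by-visit variance exceeds zero.

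Under the assumed variances, type I error runs from about 6% to 19% in one simulation. In the other it is about 9-19% with new caregivers at each visit and about 13-45% with the same caregivers throughout (100% minus coverage, s from 0.05 to 0.4). The figures differ because the caregiver term takes up part of the visit variance only when caregivers change. All of them rest on assumed variances.

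An analysis of T3 alone, or one pooled T1-T3 arm effect, is sound as it stands. The weight is moderate: this is a cheap improvement to the specification, not a demonstrated error in the primary result.

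**What to change.** State which time points enter the compliance model and which contrast is primary. Then take one of two routes:

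- **Joint model.** Add a DCC-by-time-point random intercept to the logistic model, or an unstructured DCC-level covariance over T0 to T3, alongside the caregiver level.
- **Single comparison.** Make T3 the primary comparison, with a DCC random intercept and the DCC's T0 compliance always included as a covariate, not only when judged necessary.

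Either takes a sentence or two and uses data already being collected. The cost of the first is somewhat wider intervals if visit variance is present. The cost of the second is that T1 and T2 no longer contribute to the primary comparison.
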